Previous studies reported that abnormal autonomic nervous system (ANS) might correlate with chronic pelvic pain [28]. However, to date, few objective assessment indicators have been used for evaluating autonomic nervous function in patients with CP/CPPS. This study employs, for the first time, evaluation of sympathetic skin response. The main reason for choosing this measurement is that SSR can reflect the functional state of the postganglionic fibers of the sympathetic design, although its effectiveness in evaluating CP/CPPS patients has not been systematically investigated.

The primary aims of this research are threefold: (1) to identify more relatively effective interventions for improving pain symptoms in CP/CPPS patients; (2) to ascertain the correlation between PFM elastic modulus and tenderness symptoms; this study may find a more objective method of assessing efficacy; and (3) to determine the correlation between the intensity of the sympathetic skin response and the patient’s symptoms and to explore other possible pathogenetic mechanisms.

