### Statistical methods

Statistical analysts perform data analysis in a blind state. All statistics analyses will be performed using SPSS 25.0 for Windows (SPSS Inc., Chicago, IL, USA). All data will be entered into SPSS by the research assistant. A *p*-value of < 0.05 will be considered statistically significant. One-way (3 groups: single extracorporeal shockwave therapy vs single myofascial release therapy vs combined therapy) analysis of variances (ANOVA) with repeated measures will be performed to compare changes in sEMG assessment and NIH-CPSI scores between and within groups over different time points (i.e., T0-T2). A paired sample *t*-test was used to compare the differences in outcome indicators between groups at T2 and T3 to determine the long-term efficacy of each intervention. Post hoc analyses will be performed when any significant difference both between- and within-group is found in any of the outcome variables. Bonferroni correction will be used to adjust the alpha levels. Multilevel regression or a generalized estimating equation (GEE) will also be used as a sensitivity analysis to analyze the correlation between NIH-CPSI scores and the results of sEMG assessment of the pelvic floor muscle and the results of sympathetic skin response. Mediation analysis will examine the mediating effect of sEMG assessment at T1 on the relation between extracorporeal shockwave therapy and NIH-CPSI scores at T2. This study strictly controlled for gender, age, and BMI of the participants, which may affect the primary and secondary outcomes. The mean absolute difference (MAD) and standard error of measurement (SEM) will be used to evaluate inter-method reliabilities. Consequently, Bland–Altman plots will be used to investigate the agreement between NIH-CPSI and SSR. Since the two measurement results have different measurement units, a *Z*-score will be calculated based on the formula: *Z*-score = (observation value − mean value)/SD.

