This study innovatively uses the modulus of elasticity to assess pelvic floor muscle tone, which has previously been used to assess the muscle status of spastic muscles in hemiplegic patients with good sensitivity [48, 49]. In the course of the previous treatment, it was found that the pelvic floor muscles became less stiff and more elastic after myofascial release therapy, but the improvement in elasticity has not been assessed by objective criteria.

Sympathetic skin response is a transient potential change in the skin that is triggered by endogenous or exogenous stimuli. As a noninvasive test, SSR can be used clinically to detect disorders related to sympathetic tone [50]. Due to the extensive distribution of sympathetic postganglionic fibers in the skin and the fact that the nerves in the skin of the upper limbs and chest originate from the cervical and stellate ganglia, stellate ganglion nerve activity can be reflected by upper limb skin sympathetic nerve activity. Since reduction of CP/CPPS symptoms can significantly improve depression, anxiety, and pain symptoms of patients [16], we presume the possible pathogenesis of chronic pelvic pain syndrome may be the altered sympathetic nerve function caused by anxiety and depression.

This study will compare the agreement between patients’ sympathetic skin response and NIH-CPSI scores at different stages of treatment. If the results of this study show good linear correlations, it may suggest that one of the pathogenic mechanisms of CP/CPPS is hypo- or hyper-autonomic function and that more effective combination treatments could be developed by focusing on this pathogenesis in the future. This proposed study aims to contribute to this growing area of research by exploring the pathogenesis and novel therapeutic targets of CP/CPPS.

Moreover, the study may yield a limitation: we could only realize that participants and evaluators were blinded, and the therapist would know the grouping. We will try to improve our method in the follow-up research, trying to achieve the requirement that therapists be blinded.

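### Bland–Altman limits on z-scored NIH-CPSI and SSR only restate their correlation, and would show a strong inverse association as worse agreement than none

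*Protocol article*

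**What the plan says.** The Background of the protocol article lists among its primary aims "to determine the correlation between the intensity of the sympathetic skin response and the patient’s symptoms". The stated target is therefore a correlation.

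The Statistical methods section approaches this pair in two ways:

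- **Regression.** "Multilevel regression or a generalized estimating equation (GEE) will also be used as a sensitivity analysis to analyze the correlation between NIH-CPSI scores" on one side and sEMG "and the results of sympathetic skin response" on the other.
- **Agreement.** "The mean absolute difference (MAD) and standard error of measurement (SEM) will be used to evaluate inter-method reliabilities", followed directly by the statement that "Bland–Altman plots will be used to investigate the agreement between NIH-CPSI and SSR". The z-score step is justified thus: "Since the two measurement results have different measurement units". Its formula subtracts the mean and divides by the SD ("observation value − mean value)/SD"). The section does not say whether that mean and SD are taken per visit, pooled over visits or from baseline.

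The Discussion first says that agreement between SSR and NIH-CPSI will be compared across stages of treatment. The next sentence bases the inference on something else: "If the results of this study show good linear correlations, it may suggest that one of the pathogenic mechanisms of CP/CPPS" is reduced or excessive autonomic function. Either direction would count as a finding.

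NIH-CPSI is described under the primary outcomes as a questionnaire total from 0 to 43. SSR is described under the secondary outcomes as a palmar potential evoked by stimulating the median nerve at the opposite wrist.

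**The concern.** Bland–Altman analysis asks whether two methods of measuring one quantity can replace each other. Its outputs are the bias in the units of measurement and the spread of the differences around it. A symptom questionnaire and a skin potential are not two methods for one quantity, so the question does not arise. The need to remove the units before subtracting is itself a sign that the method does not apply.

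Standardising also removes what the plot normally reports: both variables are forced to the same mean and the same SD. What is left depends on the correlation alone, and not symmetrically. Positive correlation narrows the limits and negative correlation widens them.

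At stake is the SSR aim. The trial does not know in advance whether more severe symptoms go with a larger or a smaller SSR. If the relation is inverse, the agreement output would present a strong link as the poorest result. A reader who takes that output as the evidence on autonomic involvement could conclude that there is no link when there is one.

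**Working it through.** **Inputs.** The measurement pair, the z-score formula and the choice of Bland–Altman come from Statistical methods. The two-sided autonomic hypothesis comes from the Discussion. The correlation r between NIH-CPSI and SSR is not given anywhere, so a range is assumed. The plan states no limits of agreement and no threshold, so there is no figure of its own to reproduce.

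**Algebra.** Let Zx and Zy be the two measures, each standardised in the analysed sample (mean 0, SD 1).

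1. Mean difference: 0 − 0 = 0, whatever the data.
2. Variance of the difference: 1 + 1 − 2r = 2(1−r), so the SD of the differences is √(2(1−r)).
3. 95% limits: ±1.96·√(2(1−r)).
4. Covariance of the difference with the average of the two: (1 − 1)/2 = 0, so the plot cannot show a trend of difference with level either.

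**Numbers.**

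| Assumed r | SD of differences | 95% limits (SD units) |
|---|---|---|
| +0.8 | √0.4 = 0.632 | ±1.24 |
| +0.5 | √1.0 = 1.000 | ±1.96 |
| 0 | √2.0 = 1.414 | ±2.77 |
| −0.5 | √3.0 = 1.732 | ±3.39 |
| −0.8 | √3.6 = 1.897 | ±3.72 |

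**Check by simulation.** Samples of 150 pairs were drawn at three values of r, each with two very different sets of raw means and SDs. The bias was zero to rounding error (about 1e-16). The limits matched the formula to four decimals and did not change with the raw scales: 3.7375, 2.7776 and 1.3273 for samples drawn at r = −0.8, 0 and +0.8. They differ slightly from the table because the sample correlation differs from the value drawn from.

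**Dependence on sign coding.** If SSR is multiplied by −1 before standardising, the limits become ±1.96·√(2(1+r)). At r = −0.8 they shrink from ±3.72 to ±1.96·√0.4 = ±1.24. The patients and the strength of association are the same; only the coding has changed.

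**MAD and SEM, if computed on the same z-scores.** With normal differences, MAD = SD of differences × √(2/π), and SEM = SD of differences / √2. At r = +0.8, 0 and −0.8, MAD is 0.50, 1.13 and 1.51, and SEM is 0.45, 1.00 and 1.34. The ordering is the same.

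**Other choice of reference.** If the mean and SD are pooled over T0 and T3, the overall bias is still zero, but the bias at each visit need not be. In an illustration with assumed shifts of −1 SD in one measure and +0.8 SD in the other between visits, the bias was +0.79 at T0 and −0.79 at T3. That reflects how far each measure moved in its own SD units, not agreement.

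**The case against.** The strongest reply is that the plan does not rest the autonomic question on the plot. The aim in the Background is a correlation, the Discussion's criterion is linear correlation, and no limits-of-agreement threshold appears anywhere. The planned multilevel or GEE regression covers NIH-CPSI with SSR and would report an inverse association with its sign. This stands. A reader might infer that the plan will give a wrong answer to the autonomic question; the documents do not support that. The error would arise only if someone judged the link by the agreement output.

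Three further limits also stand:

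- A reader might infer that the analysis pools differences between patients with treatment change. The documents do not say so, and the Discussion's reference to stages of treatment points rather to a comparison by visit.
- The sentence on MAD and SEM names no measurement pair. Its link to NIH-CPSI and SSR is plausible from the sentence that follows, but it is an inference.
- SSR is a secondary outcome, and the randomised treatment comparison is not touched.

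What does not stand is that the regression cures the defect. It is labelled a sensitivity analysis, and the section names no main correlation analysis for this pair. The Discussion moves from agreement to linear correlation in consecutive sentences as if they were one thing. The analysis it takes up by name is the agreement one.

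**Conclusion.** The point holds as a wrong choice of method with a real risk of misreading, not as a determined error in the trial's conclusion. With z-scores formed in the analysed sample, the planned plot carries no information beyond r and ranks a strong inverse association (±3.72 at r = −0.8) below no association (±2.77) and far below an equally strong positive one (±1.24).

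The formula is exact for standardisation within the analysed sample. The values of r are assumed. With visit-pooled standardisation only the overall bias is fixed at zero, and a bias at a single visit still says nothing about agreement. The matter deserves correction because it concerns a stated aim, but it does not affect the efficacy comparison between the arms.

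**What to change.** - In Statistical methods, delete the Bland–Altman and z-score steps for NIH-CPSI and SSR. If MAD and SEM are meant for this pair, delete them too; if they are meant for another pair, name it.
- Make the multilevel or GEE regression that is already planned the named analysis of the SSR–symptom association rather than a sensitivity analysis. Choose one of the two models, use T0 and T3, include arm and visit as covariates, and report the signed slope or correlation with its 95% CI.
- Optionally report alongside it the T0 correlation, and a regression of the T0-to-T3 change in NIH-CPSI on the change in SSR. These describe the association between patients and the association within patients respectively.
- In the Discussion, write association in place of agreement.

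Both measures are already scheduled at T0 and T3, so the cost is analysis wording only, with no new data or visits.

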## Discussion

CP/CPPS is often misdiagnosed as prostatitis and is commonly treated with antibiotics. However, in recent years, some studies have shown that pharmacological treatments do not have a significant effect and maybe even no difference from placebo [33, 34]. The pathogenesis of CP/CPPS is currently unknown. However, studies on this have mainly shown an association with the following mechanisms: (1) inflammation of the pelvic organs (prostate, bladder, uterus) and/or PFM leads to increased expression of several immunologically active mediators that act via neuronal crosstalk on the corresponding tissues, adjacent organs, and the central nervous system [35, 36]; (2) overuse and abnormal postures will activate the myofascial and thus produce permanent contraction that produces pain [37] and increase the tension even in the most relaxed state; this will prevent full elongation of the muscle [38] and thus limit the range of motion to some extent [39]; (3) inflammation within the prostate causes irritation of the prostate and peripheral nervous system in sensitive individuals and induces some pain [40]; and (4) long-term fear, tension, depression, stress, and other mental factors will lead to systemic plant nerve dysfunction [41], which increases alpha1 receptor excitability. Then, this dysfunction will cause neuromuscular dysfunction in the posterior urethra and increase urethral pressure, making it easier for urine to reflux and creating a sense of incomplete urination. One of our purposes is to determine the association between CP/CPPS symptoms and sympathetic nerves in order to explain the pathogenesis.

It is now recommended by the British Urology Association that the main aim of CP/CPPS treatment is to mitigate functional damage to patients [42], usually with single internal and external fascia manipulation. However, most of the studies on myofascial release therapy are pre-and post-controlled trials while lacking high-quality randomized controlled trials [43]. As mentioned in the literature review, myofascial release therapy can effectively alleviate the symptoms of pelvic floor pain in patients, but evidence for the intervention efficacy remains greatly inconclusive because the main primary outcome in existing studies is subjective scale [32, 44, 45]. At present, there are no studies on myofascial release therapy combined with extracorporeal shockwave therapy. Our study will compare three treatments—single myofascial release therapy, extracorporeal shockwave therapy, and combined therapy—and then propose to compare the relationship between the three treatment modalities and the subjective and objective functional changes before and after treatment.

In previous assessments, we found that the symptoms of chronic pelvic pain syndrome may be closely associated with increased pelvic floor muscle tone, which can be effectively reduced with myofascial release therapy. In this study, by comparing the association between the primary and secondary outcome measure and different therapy modalities (extracorporeal shockwave, myofascial release, and combined therapy) on the therapeutic effect of pelvic floor hypertonia at T0-T3 stage, it was proposed to determine (1) if shockwave therapy can reduce pelvic floor muscle tension further after taking myofascial release therapy; (2) if the combined therapy can reduce pelvic floor muscle tone, relieve the discomfort symptoms, and improve the quality of life of the patients more efficiently and have a long-term effect than single treatment [46, 47]; (3) if curative effect can be reflected by the change of sympathetic skin response before and after treatment; and (4) if there exist other mechanisms that may improve the symptoms of patients other than what extracorporeal shockwave and myofascial release therapy did on reducing pelvic floor muscle tone.

This study innovatively uses the modulus of elasticity to assess pelvic floor muscle tone, which has previously been used to assess the muscle status of spastic muscles in hemiplegic patients with good sensitivity [48, 49]. In the course of the previous treatment, it was found that the pelvic floor muscles became less stiff and more elastic after myofascial release therapy, but the improvement in elasticity has not been assessed by objective criteria.

Sympathetic skin response is a transient potential change in the skin that is triggered by endogenous or exogenous stimuli. As a noninvasive test, SSR can be used clinically to detect disorders related to sympathetic tone [50]. Due to the extensive distribution of sympathetic postganglionic fibers in the skin and the fact that the nerves in the skin of the upper limbs and chest originate from the cervical and stellate ganglia, stellate ganglion nerve activity can be reflected by upper limb skin sympathetic nerve activity. Since reduction of CP/CPPS symptoms can significantly improve depression, anxiety, and pain symptoms of patients [16], we presume the possible pathogenesis of chronic pelvic pain syndrome may be the altered sympathetic nerve function caused by anxiety and depression.

This study will compare the agreement between patients’ sympathetic skin response and NIH-CPSI scores at different stages of treatment. If the results of this study show good linear correlations, it may suggest that one of the pathogenic mechanisms of CP/CPPS is hypo- or hyper-autonomic function and that more effective combination treatments could be developed by focusing on this pathogenesis in the future. This proposed study aims to contribute to this growing area of research by exploring the pathogenesis and novel therapeutic targets of CP/CPPS.

Moreover, the study may yield a limitation: we could only realize that participants and evaluators were blinded, and the therapist would know the grouping. We will try to improve our method in the follow-up research, trying to achieve the requirement that therapists be blinded.

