### Eligibility criteria

Patients with hormone abnormalities are excluded because thyroid dysfunction and testosterone may affect prostate function and myofascial status.

Participants will be screened using the following criteria.

Inclusion criteria:According to the National Institutes of Health classification of prostatitis [29], all male patients meet the diagnostic criteria for chronic prostatitis type IIIB/chronic pelvic pain syndrome (pain in the bladder, groin, perineal area, genitalia or lower abdomen with no significant abnormalities on urological examination);Patients are aged 20–40 years;Patients with chronic pelvic pain lasting over 6 months;Patients sign the informed consent form.

Exclusion criteria:Patients with significant coagulation disorders, perineal anatomical abnormalities, hormonal abnormalities, and neurological abnormalities;Patients with an apparent cause of pelvic pain, such as a history of previous surgery, chronic infection, trauma, prostatitis, and epididymitis;Patients receiving other treatments during the study;Patients with any urethral pathology;Patients who have had closed lumbar injections and previous lumbar surgery within 6 months;Patients with other conditions causing pelvic pain;Patients with contraindications to physiotherapy;BMI > 22.9

Termination and shedding criteria:Other serious illnesses occur in the course of treatment;Poor patient adherence and failure to complete the full course of treatment.

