#### Secondary outcome measures

Three-dimensional quantification and shear wave elastography (SWE).

Trans-rectal three-dimensional ultrasound (VOLUSON E8) will be used to assess the morphological parameters of the lacunae of the levator hiatus in CP/CPPS patients. The area of the levator hiatus is situated at a depth of 2–4 cm from the perineum, which is well within the effective range of 7–4-MHz transducers. The plane of minimal anteroposterior (AP) diameters will be identified in the mid-sagittal image; at this level, the axial plane will be then utilized to determine the minimum AP and lateral diameters of the levator hiatus as well as the hiatal area. After B-mode sonographic evaluation, shear wave elastography will be activated. Shear wave elastography will be used to assess the modulus of elasticity of the pubovisceral muscle (attaching laterally to the perineum) in patients with CP/CPPS. The propagation velocity of shear waves is proportional to the elastic modulus of tissue. By measuring the velocity of shear waves, the hardness of tissue can be measured directly [30]. The stiffness of the tissue will be displayed in color code rectangle.

(2)Sympathetic skin response (SSR).

SSR is a recently established method of noninvasive somatic neurography that offers the advantages of both non-invasiveness and specificity, using the SA7550 FlexComp Infiniti System (Thought Technology, Canada).

Sympathetic skin responses will be recorded with the active electrodes placed in the left palm and the reference electrodes placed on the dorsum of the left hand while the patient is in the sitting position. A channel recording from the hand will be obtained simultaneously via stimulation of the contralateral median nerve at the level of the wrist with a stimulation intensity of 20 mA for 0.2 ms [31]. Three potentials will be recorded, and the mean values will be used for analysis.

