## Data collection and management

### Plans for assessment and collection of outcomes

Three groups of participants will be treated by trained therapists, and the intervention process will be strictly in accordance with the study protocol. The Primary outcome measurements will be carried out at T0, T1, T2, and T3. Secondary outcome measurements will be carried out at T0 and T3. Equipment used in the assessment, such as pelvic floor biofeedback electrostimulation, pelvic floor ultrasound, and sympathetic skin response devices, will be operated by the same researchers, and the type of equipment and the assessment site will remain the same.

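### A correlation between sympathetic skin response and NIH-CPSI can be estimated here, but it cannot support the autonomic-mechanism reading that the Discussion attaches to it

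*Protocol article*

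**What the plan says.** The protocol article makes pathogenesis a purpose in several places. The abstract says it will be analysed through the intercorrelation of the subjective and objective measures. The third primary aim in the Background is "to determine the correlation between the intensity of the sympathetic skin response and the patient’s symptoms and to explore other possible pathogenetic mechanisms". The Discussion adds: "One of our purposes is to determine the association between CP/CPPS symptoms and sympathetic nerves in order to explain the pathogenesis".

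The Discussion also states in advance how a result would be read. Given good linear correlations between SSR and NIH-CPSI, "it may suggest that one of the pathogenic mechanisms of CP/CPPS is hypo- or hyper-autonomic function", and combination treatments might later be built on this. It names a presumed cause: "we presume the possible pathogenesis of chronic pelvic pain syndrome may be the altered sympathetic nerve function caused by anxiety and depression".

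On measurement, the section on secondary outcome measures says of SSR: "Three potentials will be recorded, and the mean values will be used for analysis". On timing, the section on plans for assessment says: "Secondary outcome measurements will be carried out at T0 and T3". Study design repeats this limit, but an earlier sentence in that section lists SSR among assessments at all four time points.

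On analysis, Statistical methods plans Bland–Altman agreement of Z-scores for NIH-CPSI and SSR, and a multilevel model or GEE for the correlation of NIH-CPSI with sEMG and SSR. The only mediation model uses sEMG at T1.

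**The concern.** The stated reading goes from a linear association to a mechanism of disease. For that step the association would have to show three things: that SSR is abnormal in a given direction, that SSR acts on symptoms and not the reverse, and that no common cause explains both. A correlation among treated patients shows none of these.

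Because either under- or over-activity is accepted, a correlation of either sign could be taken as support. The premise offered for the presumed cause is that relieving symptoms improves depression and anxiety. That runs from symptoms to mood, the opposite of the chain proposed.

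At stake is what the trial may conclude about mechanism. A correlation with several equally good explanations could be reported as pointing to an autonomic cause and used to motivate later treatments.

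**Working it through.** The protocol gives no figure for the SSR correlation, so there is none to reproduce. Its only power figure, 40 per group for d = 0.5 at 60% power, does reproduce (two-sided t-test power 59.8%), but this point does not rest on it. All correlations and shifts below are assumptions used to show what the planned analysis can and cannot distinguish.

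**1. Level of SSR.** For any constant c, corr(S + c, Y) = corr(S, Y). With an assumed r = 0.40, moving all SSR values by +3 SD or by −3 SD left r at 0.40. Low, normal and high SSR are therefore indistinguishable by this criterion. All three arms are treated patients, so there is no unaffected group for comparison. The article gives limits for sEMG (4, 35 and 30 μV by phase) but none for SSR. Even with a normal range, the information would lie in the level, not in the correlation.

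The Bland–Altman analysis does not help. If both measures are converted to Z-scores within the same sample, the mean difference is 0 by construction and the variance of the difference is 2(1 − r). The plot then adds nothing to r.

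**2. Direction and common cause.** Three structures were simulated with standardised variables:

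| Structure | Correlation of SSR with symptoms |
|---|---|
| SSR drives symptoms: Y = 0.4S + √(1 − 0.16)·e | 0.40 |
| Symptoms drive SSR: S = 0.4Y + √(1 − 0.16)·e | 0.40 |
| Anxiety A drives both: S and Y each = √0.4·A + √0.6·e | 0.40 |

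In the third structure the correlation falls to 0.00 once A is held fixed. That step needs a measure of anxiety or depression. The listed outcomes are sEMG, NIH-CPSI, three-dimensional ultrasound, elastography and SSR. The variables said to be controlled are gender, age and BMI.

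**3. Shared trend, if visits are combined without a visit term.** Suppose there is no SSR–symptom association within a visit and the T0-T3 mean shifts are d1 and d2 in SD units. With equal numbers at both visits, the combined correlation is

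r = (d1·d2/4) / √[(1 + d1²/4)(1 + d2²/4)].

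- d1 = d2 = 0.5: 0.0625/1.0625 = 0.06
- d1 = 1.5, d2 = 0.5: 0.1875/√(1.5625 × 1.0625) = 0.1875/1.288 = 0.15
- d1 = d2 = 1: 0.25/1.25 = 0.20 (simulation: 0.196)

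Correlating individual change with individual change removes this artefact, because a shift common to all patients drops out. A term for arm removes shifts that differ by arm.

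**The case against.** The strongest reply is that the text is hedged and exploratory. It speaks of what a result may suggest, of one mechanism among others, and of treatments that could follow. A reader might infer that the plan treats a correlation as proof of cause; it does not say so. A reader might also infer that the whole third aim cannot be answered. That goes too far, since its descriptive half, the correlation itself, can be estimated.

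Other stronger readings also fail:

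- **Shared trend as an expected result.** The plan does not say that visits will be pooled or that visit and arm will be left out. Model terms are commonly fixed in an SAP, which is not shown. The shifts are assumed, and at 0.5 SD the effect is negligible. This is a risk to close, not a forecast.
- **Missing normal range as an omission.** The article is condensed and a range may sit in the full protocol. The argument on level does not depend on it.
- **SSR only concurrent with symptoms.** SSR at T0 precedes NIH-CPSI at T1 to T3, and one sentence lists SSR at all four times. The narrower statements favour T0 and T3. No lagged SSR analysis is described, and one would still be confounded.
- **Restricted range.** The exclusion of patients with "hormonal abnormalities, and neurological abnormalities" might be thought to narrow the spread of SSR. Nothing in the document shows this, and a narrower range would weaken a correlation, not create one.

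What the reply does not remove is the mismatch between criterion and reading. Hedging does not help a criterion that gives the same value under the hypothesis and under its rivals.

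**Conclusion.** The point holds as a limit on interpretation. The SSR–NIH-CPSI correlation can be estimated, but it cannot support the reading that autonomic under- or over-activity is a mechanism of CP/CPPS. Nor can the trial support anxiety and depression as the cause, because neither is among the listed outcomes. These conclusions follow from the properties of a correlation and from the outcome list; the assumed r = 0.40 is only an example.

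The shared-trend figures (about 0.06 to 0.20) are conditional on assumed shifts and on a model without a visit term, and they are not needed for the main conclusion. SSR is a secondary outcome, so the primary outcomes and randomised comparisons are untouched. The change should still be made, because it alters what the trial can claim and costs little.

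**What to change.** - State the SSR aim in the Background as exploratory association. In the abstract and the Discussion, remove the autonomic mechanism and the anxiety/depression mechanism as conclusions of this trial.
- Estimate the association in two ways: across patients at T0, and as T0-T3 change in SSR against T0-T3 change in NIH-CPSI.
- In the GEE or multilevel model already planned, include arm, and include visit wherever visits are combined.
- Reconcile the Study design sentence that lists SSR at all four time points with the statements there and under plans for assessment that limit secondary outcomes to T0 and T3.

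This needs changes of wording and two model terms, with no new data. The price is a weaker mechanistic claim. Change-on-change association removes the shared trend but still does not establish direction, so it should be reported as association.
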